### RATIONALE FOR CURRENT STUDY

Recent infectious disease outbreaks, including the COVID-19 pandemic, have emphasized the critical need for rapid development of effective vaccines. However, recognised variation in immune responses after vaccination across populations in different countries poses a barrier to progress, and it has yet to be determined whether this variation is due to differences in genetic background, in environmental influences including past or persistent antigenic exposure, and/or other poorly defined mechanisms. Despite this known variation, the majority of mechanistic studies investigating immune responsiveness to vaccines have focused on populations of white European ancestry. In the UK, this underrepresentation of ethnic minorities in vaccine experimental medicine research is at least partly due to vaccine hesitancy amongst these groups.

A further challenge in addressing differences in vaccine response across populations is that studies have traditionally focused on the use of peripheral blood samples, even though inflammatory and germinal centre (GC) responses mounted in the draining LNs likely dictate vaccine priming efficiency and underpin protective efficacy. Ultrasound (US) guided FNA is a tractable and safe approach for LN sampling, and its use has recently demonstrated a good representation of cell subtypes found in excisional biopsies, including GC cells, thereby opening invaluable new routes for assessing vaccine efficacy in humans in vivo.

The LEGACY01 clinical study will address this by creating a dataset of unstimulated and stimulated in vivo immune responses to a model, seasonal influenza vaccine, from participants with African and Asian ancestry.

### ROLE OF THE PARTNER INSTITUTIONS

Imperial College London is the Sponsor for the study. Recruitment and study visits will be at the NIHR Imperial Clinical Research Facility, Hammersmith Hospital, [name].

Imperial College London and Imperial CRF will manage the study. The University of Oxford will receive and process samples and run laboratory analysis of blood and lymph node tissues led by [name] at the Wellcome Centre for Human Genetics. The Uganda Virus Research Institute will support establishment of a framework for delivering single-cell vaccine studies at international sites such as Uganda. Specifically, they will appoint and support the training of a visiting Clinical Research Fellow to the UK at Imperial College London and the University of Oxford. All centres will support the patient and public involvement and engagement activities of the study.

## **HUMAN CELL ATLAS**

LEGACY01 is one of the Ancestry Networks for the Human Cell Atlas funded by the Chan Zuckerberg Initiative. The goal of these networks is to generate single-cell data from ancestrally diverse tissue samples, which will be uploaded and made available as open access research data for the Human Cell Atlas.

## **STUDY AIM, OBJECTIVES AND OUTCOME MEASURES**

The aim of the study is to investigate human immune responses in lymph node cells before and after immunisation with a seasonal influenza vaccine

Primary objective: To generate a single cell atlas of lymph node cells before and after immunisation with seasonal influenza vaccine.

Secondary objective: To compare serum antibody responses before and after immunisation.

Exploratory: To compare immune responses in various immune compartments (e.g., blood and lymph nodes) against antigens including influenza before and after immunisation to help inform vaccine development and testing across different ethnicities.

Capacity building and training: To build capacity with respect to staff expertise and resource between the three partner institutions to support this project and future similar research.

Outcome measures may include but are not limited to the following assays:

1. Single cell RNA sequencing analysis of LNC and matched paired PBMC
2. Binding ELISA specific for influenza/A antigens e.g., haemagglutinin
3. Intracellular cytokine secretion or activation induced marker assay of PBMC and LNC
4. Genotypic assays such as HLA-testing.

## **7. STUDY DESIGN**

Interventional experimental medicine study using a model vaccine, seasonal influenza vaccine, as a probe to stimulate the immune system in vivo with sampling to collect serum, plasma, PBMC and LNC at specified time points pre and post immunisation. The study is single arm, non-randomised and open label.

Duration: Three years

Number and type of subjects: Thirty healthy adult volunteers of African or Asian ancestry will be enrolled. Participants may enrol into either cohort 1 (influenza season 2022-2023) or cohort 2 (influenza season 2023-2024).

Study intervention: A single dose of a licensed seasonal influenza vaccine will be administered intramuscularly into the deltoid muscle. See Appendix 1 for (2021-2024) recommendations for seasonal influenza vaccines in the UK.

## **INFLUENZA VACCINE**

The influenza vaccine of choice for this study is adjuvanted quadrivalent influenza vaccine (aQIV), also marketed as Flud Tetra (Seqirus UK Ltd). One 0.5 mL dose of aQIV contains 15 micrograms of haemagglutinin from two A and two B strains of influenza propagated in hens' eggs. It is adjuvanted with MF59C.1 which contains per 0.5ml dose, squalene (9.75 mg), polysorbate 80 (1.175 mg), sorbitan trioleate (1.175 mg), sodium citrate (0.66 mg) and citric acid (0.04 mg).

Clinical studies have been conducted in individuals aged 65 years and over and in children aged 6 months to 6 years. In studies V118\_20 and V118\_18, n=4269 subjects aged 65 years and older were vaccinated. AEs were injection site pain (16.3% and 31.9%), fatigue (10.5% and 16.0%) and headache (10.8% and 12.0%) and resolved within three days. In the first study, during the 2017-2018 Northern Hemisphere influenza season Flud Tetra met non-inferiority for influenza A/H1N1, A/H3N2, B/Yamagata and B/Victoria and superiority for the B strains not included in the Flud aTIV comparators, aTIV-1 and aTIV-2

Study V118\_05 assessed Flud Tetra in children aged 6 months to 6 years and elicited a higher immune response than the non-adjuvanted vaccine that persisted to 12 months. A higher incidence of local and systemic reactions was reported. Although acceptable immunogenicity was reported, the vaccine did not meet its primary efficacy endpoint in this paediatric study.

Safety and immunogenicity data of Flud, the trivalent formulation, is relevant for aQIV because they have similar compositions and are manufactured in the same way. Post marketing surveillance data are not available yet for aQIV but are available for Flud and are detailed in Appendix 3.

The aQIV is licensed for clinical use in patients aged 65 years and over due to its immunogenicity profile in this age group. Coupled with the paediatric data, it is expected that this vaccine will deliver high titres of influenza-specific antibody at least equivalent to the unadjuvanted vaccine which includes 15 µg of haemagglutinin per strain and which is currently widely used in younger adults. aQIV contains haemagglutinin from four strains of influenza virus. As a result, participants choosing to enter this study during the Northern hemisphere influenza season and who receive the study vaccine are not expected to be disadvantaged compared with individuals who receive an influenza vaccine through the NHS.

An adjuvanted vaccine is chosen for this experimental medicine study in order to investigate lymph node responses to immunisation where the adjuvant will stimulate a local innate response. It is expected that swelling of the cortex will be visible using greyscale (or conventional) US. The published safety and tolerability profile of aQIV is in line with expected responses for an influenza vaccine. A similar safety and tolerability profile is expected in adults aged 18 – 55 years.

Participants will undergo a fine needle aspiration of a suitable axillary lymph node on two occasions with an optional third visit for up to n=6 cohort 2 only at sites ipsilateral and contralateral to the site of injection.

## 8. PARTICIPANT ENTRY

### PRE-REGISTRATION EVALUATIONS

Participants will attend a screening visit and provide written informed consent to enrol onto the study.

### PARTICIPANT INCLUSION CRITERIA

- Healthy adults aged 18 years to 55 years on the day of screening
- Willing and able to provide written informed consent
- Identifies as having African or Asian ancestryi
- Usually resident in the UK for at least 5 years prior to screening
- If female and of childbearing potentialii not pregnant on the day of screening and willing to use a highly effective form of contraception until 12 weeks after the study immunisationiii.
- Willing to avoid all other vaccines within 4 weeks either side of the study injection and fine needle aspirationiv.
- Willing and able to comply with the visit schedule and provide samples.
- Willing to grant authorised persons access to his/her trial related medical record and GP records either directly or indirectly.

i A list of ethnic groups in the UK is available at [List of ethnic groups - GOV.UK \(ethnicity-facts-figures.service.gov.uk\)](https://www.gov.uk/government/statistics/list-of-ethnic-groups-in-the-uk).

ii A woman will be considered of childbearing potential following menarche and until becoming post-menopausal unless permanently sterile. Permanent sterilisation methods include hysterectomy, bilateral salpingectomy and bilateral oophorectomy. A post-menopausal state is defined as no menses for 12 months without an alternative medical cause.

iii Highly effective forms of contraception include medical sterilisation of a woman or her partner, hormonal methods of contraception that prevent ovulation and intrauterine devices or systems. Barrier methods of contraception are not considered highly effective. Abstinence should be the preferred and usual lifestyle of the participant.

iv An exception is made for authorised or licensed COVID-19 vaccination according to national clinical directives. A gap of at least 28 days either side of an FNA is preferred but where there is clinical imperative a shorter gap is acceptable. Where a COVID-19 vaccine is scheduled near to an FNA, the FNA should occur before the vaccination where possible.

### PARTICIPANT EXCLUSION CRITERIA

- Pregnant or lactating
- Has a significant clinical history, physical finding on clinical examination or laboratory finding during screening, or presence of a disease that is active or requires treatment to control it,

including cardiac, respiratory, endocrine, metabolic, autoimmune, liver, neurological, oncological, psychiatric, immunosuppressive/immunodeficient or other disorders which in the opinion of the investigator is not compatible with healthy status, may compromise the volunteer's safety, preclude vaccination or tissue sampling or compromise interpretation of the immune response to vaccine. Individuals with mild/moderate, well-controlled comorbidities are allowed.

- Body mass index of 35 or greater
- History of anaphylaxis or angioedema
- History of severe or multiple allergies to drugs or pharmaceutical agents or contraindicated from receiving influenza vaccine or local anaesthetic including lidocaine.
- History of severe local or general reaction to vaccination defined as:

local: extensive, indurated redness and swelling involving most of the arm, not resolving within 72 hours

general: fever  $\geq 39.5$  °C within 48 hours; bronchospasm; laryngeal oedema; collapse; convulsions or encephalopathy within 72 hours

- Receipt of any immunosuppressive agents within 18 weeks of screening by any route other than topical
- Prescribed regular blood thinning medication likely to induce bruising or bleeding on fine needle aspiration
- Detection of antibodies to hepatitis C
- Detection of antibodies to HIV
- Detection of anti-hepatitis B core antibodies
- Participating in a clinical trial with an investigational drug or device or treated with an investigational drug within 28 days of screening.

## **WITHDRAWAL CRITERIA**

Participants are free to withdraw from the study at any time and for any reason without prejudicing their usual medical care.

Discontinuing sample donation: those participants who choose to discontinue lymph node tissue donation can be followed up to donate blood samples. Those participants where the investigator chooses to discontinue tissue donation can be followed up to donate blood samples.

Participants who choose to discontinue all (blood and lymph node) sample donation will be withdrawn from the study once the investigator deems it safe to do so.

Withdrawing from vaccination: Those participants who choose not to, or are unable to, have an influenza vaccine as part of the study schedule can continue to provide lymph node and blood samples.

Additional volunteers may be enrolled to replace withdrawn participants or those who are unable to complete the study schedule of visits per protocol for any reason.

**COENROLMENT GUIDELINES**

Participants will be entered into the TOPS database to prevent over-volunteering. Co-enrolment into another study is discouraged but can be allowed at the discretion of the investigator where neither the safety of the participant nor the integrity of the data is at risk. An example would be co-enrolment into an observational study with either no sampling or a low volume blood draw.

**9. ADVERSE EVENTS****DEFINITIONS**

Adverse Event (AE): any untoward medical occurrence in a patient or clinical study subject.

Serious Adverse Event (SAE): any untoward medical occurrence or effect that:

Results in death

Is life-threatening – refers to an event in which the subject was at risk of death at the time of the event; it does not refer to an event which hypothetically might have caused death if it were more severe

Requires hospitalisation, or prolongation of existing inpatients' hospitalisation

Results in persistent or significant disability or incapacity

Is a congenital anomaly or birth defect

Medical judgement should be exercised in deciding whether an AE is serious in other situations. Important AEs that are not immediately life-threatening or do not result in death or hospitalisation but may jeopardise the subject or may require intervention to prevent one of the other outcomes listed in the definition above, should also be considered serious.

**REPORTING PROCEDURES**

Adverse events should be reported depending on the nature of the event and the reporting procedures below should be followed. Any questions concerning adverse event reporting should be directed to the Chief Investigator in the first instance. Events should be graded according to the FDA: Toxicity Grading Scale for Healthy Adult and Adolescent Volunteers Enrolled in Preventive Vaccine Clinical Trials, taking account of local laboratory reference ranges.

<https://www.fda.gov/media/73679/download>

**NON-SERIOUS AES**

These will be recorded in the following instances:

Those occurring in the 5 days following lymph node tissue sampling

Those occurring in the 28 days following influenza vaccination

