**Table 1. Schedule of investigations, treatments, and assessments**

| Study visit                                                    | V1                   | V2                  | V2a                  | V3            | V4                 | V5                 | V6                                       | V6a                  |
|----------------------------------------------------------------|----------------------|---------------------|----------------------|---------------|--------------------|--------------------|------------------------------------------|----------------------|
| Visit location                                                 | Site                 | Site                | Remote
(by phone) | Site          | Site               | Site               | Site                                     | Remote
(by phone) |
| Visit type                                                     | Screening            | Enrolment:
FNA 1 | Follow up            | Vaccination   | Follow-up:
FNA2 | Follow up          | Optional follow up
FNA 3  | Follow up            |
| Study week                                                     | minus 24 to minus 1  | 0                   | 0                    | 1             | 2                  | 5                  | 7                                        | 7                    |
| Study day                                          | minus 168 to minus 1 | 0                   | 5                    | 7             | 12                 | 35                 | 49                                       | 54                   |
| Window (days)                                                  | NA                   | NA                  | minus 1 to plus 1    | 0 to plus 161 | minus 2 to plus 2* | minus 2 to plus 14 | minus 2 to plus 28                       | minus 1 to plus 1    |
| Informed consent                                               | x                    |                     |                      |               |                    |                    |                                          |                      |
| Demographics                                                   | x                    |                     |                      |               |                    |                    |                                          |                      |

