3. At visits which include FNA or vaccination, there will be an AE check and vital signs pre-FNA/pre-vaccination, and again at least 30 min after. At visits which include FNA, there will be an inspection of the FNA site pre-FNA, and again at least 30 min after. All other procedures/assessments at these visits will be pre-FNA/pre-vaccination only.
4. The timings of V2a and V3 are set according to that of V2; the timings of V4, V5 and V6 are set according to that of V3.
5. Optional third FNA for up to n=6 cohort 2 participants only at 6 weeks post vaccination followed by a final phone visit to discuss any AEs.
6. A paper survey at visit 5 for cohort 2 only to collect information on participant's experience.

\* This is the preferred window. However, if the FNA2 visit cannot be scheduled within the preferred window, it can take place up to 21 days after the vaccination without being a protocol deviation. Every effort should be made to schedule the FNA2 visit as close to 5 days post-vaccination as possible.

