**STUDY ASSESSMENT SCHEDULE**

Participants will be followed up according to the study schedule in Table 1. Participants will attend a screening visit at the study site, and they will be asked to provide proof of identity at the visit. Written informed consent will be obtained from participants before undergoing study procedures. The visits in the study assessment schedule are a screening visit (V1), an enrolment visit at which the first FNA will be performed (V2), a vaccination visit (V3), a follow-up visit at which the second FNA will be performed (V4) and a final follow-up visit (V5). In addition, participants will be contacted by telephone (V2a) a few days after the first FNA at V2. For a small number of participants in cohort 2 (up to n=6) there will be an option of a third FNA visit at 6 weeks post vaccination.

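### The permitted visit windows let the last adverse-event check fall before the protocol's own recording periods end (up to 2 of 28 days at V5, 1 of 5 at V6a), and FNA2 alone has no early check

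*Protocol*

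**What the plan says.** Protocol section 9, under non-serious AEs, defines two recording periods: "Those occurring in the 5 days following lymph node tissue sampling" and "Those occurring in the 28 days following influenza vaccination". The first applies to every aspirate alike.

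The contacts that could capture these events are in section 4, Table 1, which schedules an AE check at V2, V2a, V3, V4, V5, V6 and V6a.

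- **V5** has the window "minus 2 to plus 14" around study day 35. Section 10 describes it as the final follow-up visit.
- **V6**, the optional third aspirate, has "minus 2 to plus 28" around study day 49. Footnote 5 limits it to 6 participants in cohort 2 and says it is "followed by a final phone visit to discuss any AEs".
- **V2a and V6a**, the two telephone contacts, each have "minus 1 to plus 1".
- **Anchoring.** Footnote 4 times V2a and V3 from V2, and then states that "the timings of V4, V5 and V6 are set according to that of V3". It does not mention V6a.
- **Calls after aspirates.** Section 10 says that "participants will be contacted by telephone (V2a) a few days after the first FNA at V2". V6a does the same for the third aspirate. No call is listed after V4, where the second aspirate (FNA2) is taken.
- **FNA2 timing.** The note under Table 1 allows V4 up to 21 days after vaccination if the preferred window cannot be met.

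**The concern.** A recording period is only as good as the contacts that ask about it. If the last scheduled check may properly take place before the period ends, some participants who follow the protocol exactly will have days on which nobody asks about events. The AE listing will still present those days as covered.

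The second aspect is uneven timing. Section 9 sets one 5-day period for all aspirates. FNA1 and FNA3 each have a call at about its end, while FNA2, which all participants are due to have, does not. Appendix 2 lists pain or tenderness, minor bleeding and bruising as the expected events, and expects bruising to have faded after 2 weeks. If the next check comes later than that, such events can only be recovered from memory.

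What is at stake is the completeness and timeliness of AE recording. No efficacy or immunological analysis depends on it.

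**Working it through.** **Inputs** (Table 1 and its footnotes, in study days): V2 = 0, V2a = 5, V3 = 7, V4 = 12, V5 = 35, V6 = 49, V6a = 54. The day of vaccination or aspiration is counted as day 0, and a check on the last day of a period is taken to cover that day.

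**Nominal schedule.** V5 − V3 = 35 − 7 = 28 days. V2a − V2 = 5 − 0 = 5 days. V6a − V6 = 54 − 49 = 5 days. At nominal days, V5 and the two calls match the 28-day and 5-day periods exactly. Any gap therefore comes from the permitted windows.

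**28 days after vaccination.**
- V5 is allowed from 28 − 2 = 26 to 28 + 14 = 42 days after vaccination.
- Shortfall at the earliest compliant V5: 28 − 26 = 2 days (days 27 and 28).
- Participants who have V6 are seen again no earlier than (49 − 7) − 2 = 40 days after vaccination, so their period is closed by a later check.
- V6 is offered to at most 6, so V5 is the last contact for at least 30 − 6 = 24 of 30.

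**5 days after each aspirate.**

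| Aspirate | First check after the day of the procedure | Check that closes the period | Shortfall |
|---|---|---|---|
| FNA1 (V2) | V2a, day 4 to 6 | V3, day 7 or later | none |
| FNA2 (V4) | V5 | V5 | none, but late |
| FNA3 (V6) | V6a, day 4 to 6 | V6a (no later contact) | up to 5 − 4 = 1 day |

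**FNA2 in detail** (days after vaccination).
- V4 is nominally on day 12 − 7 = 5, preferred 3 to 7, permitted to 21. V5 is on day 26 to 42.
- Nominal gap from V4 to V5: 28 − 5 = 23 days.
- V4 in its preferred window: 26 − 7 = 19 to 42 − 3 = 39 days.
- With the permitted extension: 26 − 21 = 5 to 42 − 3 = 39 days.
- The FNA2 period ends on day 21 + 5 = 26 at the latest, and V5 is never before day 26. V5 therefore always falls at or after the end of the period.
- With V4 in its preferred window, V5 is at least 19 days after FNA2. That is beyond the 2 weeks (14 days) after which Appendix 2 expects bruising to have faded.

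**The case against.** The strongest reply has four parts.

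*FNA2 is covered.* Section 9 defines which events count by when they occur and does not require a contact on day 5. V5 always comes at or after the end of the FNA2 period. This stands. A reader might infer from the missing call that the period after FNA2 goes unobserved. The visit windows do not support that: the issue is late recall.

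*The difference between aspirates has a rationale.* V3 may be held up to 161 days late, so FNA1 needs its own call. FNA3 has no later visit, so it needs one too. FNA2 plus 5 days lies inside the 28-day period that V5 reviews for everyone. This is reasonable, although the protocol does not state it. It makes a call after V4 an improvement and not the correction of an error. FNA2 is also not without safeguards: an AE check and site inspection take place at least 30 minutes after the procedure, participants receive written information on expected events, and serious AEs are recorded throughout the study.

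*Nothing inferential is affected.* Section 10 says that the study has no safety-related objectives and that safety assessment serves only to protect participants. A reader might infer that events after FNA2 will look rarer than after FNA1, or that the required toxicity grading becomes unreliable. No such comparison is planned, and the content of the grading scale is not in the document, so neither inference can be sustained.

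*The V6a anchor is a clerical gap.* Because footnote 4 omits V6a, one could time it from V3, at 47 ± 1 = 46 to 48 days after vaccination. With V6 at 40 to 70 days, the call would then fall anywhere from 46 − 70 = 24 days before FNA3 to 48 − 40 = 8 days after it. Footnote 5 rules this out by placing the call after the third aspirate. What remains is an omission in footnote 4.

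None of this removes the shortfalls at V5 and V6a, which arise in fully compliant participants.

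**Conclusion.** The point holds and is minor. The recording periods in section 9 and the visit windows in Table 1 do not agree at their edges. The last scheduled check may come up to 2 days before the end of the 28-day period, for any of at least 24 of 30 participants. It may also come 1 day before the end of the 5-day period after FNA3, for at most 6. Both gaps occur only when a visit is held early within its window. Footnote 4 also lacks an anchor for V6a, although footnote 5 implies it.

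Separately, the first AE check after the day of FNA2 comes nominally 23 days later (19 to 39 days in the preferred V4 window, 5 to 39 with the extension), against 4 to 6 days after FNA1 and FNA3. The consequence is incomplete or late AE recording, with no bias in any endpoint.

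This rests on 30 participants as planned, and on counting the 28 and 5 days from the day after the procedure. If the day of the procedure were counted as the first day, the periods would end on days 27 and 4. The V5 shortfall would then be 27 − 26 = 1 day and the V6a shortfall 4 − 4 = 0. The protocol does not spell out which count applies.

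**What to change.** - Reconcile section 9 with Table 1 and its footnotes so that the last scheduled AE check cannot precede the end of the recording period. The direct way is to have no negative lower limit for V5 and V6a. V5 would then fall 28 to 42 days after vaccination and V6a 5 to 6 days after FNA3, and both shortfalls become zero.
- State in footnote 4 that V6a is timed from V6.
- As an inexpensive improvement, consider a short telephone AE check after V4 to match V2a and V6a, so that local events after FNA2 are asked about while still fresh.

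The cost is 2 days of scheduling flexibility at V5 and 1 day at V6a, one footnote entry and, if the call is adopted, about 30 short telephone contacts. No extra site visit or sample is needed.
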